### 7.3.5 Grafting

For each patient, one to two grafts (graft size:  $45 \pm 4 \text{ cm}^2$ ; graft thickness: 0.5 – 2 mm) are manufactured by tissue engineering. One produced graft has a size of  $7 \times 8 \text{ cm}^2$  of which a strip of  $1 \times 7 \text{ cm}^2$  is removed for quality analyses, which leads to a final graft size of  $45 \pm 4 \text{ cm}^2$ . The grafts are manufactured in a GMP facility and are provided on the scheduled day of skin grafting or maximally two days before in a transport medium filled tissue culture flask. Identity of the product and patient is guaranteed by the GMP compliant labelling and traceability process according to EU Directive 1394/2007 (Article 11-12 and Appendix III) and the GMP Guide Annex 13 (Chapter “Labelling”, Article 26.-33).

After successful tissue-engineering of the autologous dermo-epidermal skin-graft, EHSG-KF is grafted by a routine skin grafting procedure. During the same operation the control area is covered with a STSG meshed with a 3:1 expansion ratio (see chapter 3.6). The surgery takes place in the operating theatre of the respective study centre or accordingly qualified operating theatre and is performed by the PI and/or the Investigator under routine sterile conditions. General anaesthesia or analgosedation is performed, depending on the patient, in accordance with the standards for skin grafting procedures at the study sites. Dermal templates are not allowed in the control nor the experimental area for methodological reasons.

Wound bed preparation, grafting, and postoperative wound management will be carried out in accordance with plastic surgical principles and standards that are widely understood and implemented at the study sites. More specifically, routine standardised preoperative procedures, including disinfection, are performed. The wound dressing is removed, along with the allograft that was providing temporary coverage (if applicable), and the skin defect is revealed. Meticulous wound bed preparation is then carried out, with surgical removal of all devitalized, grossly contaminated tissues, followed by haemostasis and further disinfection to create an optimal wound bed to support the graft.

Allocation of the treatment to the two study areas, the experimental and control areas, is performed as described in chapter 3.7. Before and after wound bed preparation, and prior to grafting of the EHSG-KF or meshed STSG, facultative biopsies can be taken from each study area for histological examination of the wound ground.

The surface area (cm^2) of donor skin harvested for coverage of the control area must be determined intra-operatively and recorded, as this value will be used for the calculation of the primary endpoint (ratio of covered surface area to donor site surface area, as per chapter 8.1). Application of the study product and the meshed STSG will then be carried out in accordance with the standard method for split-thickness skin graft application, taking care to ensure the grafts are correctly oriented with keratinocytes facing upwards. In an effort to reduce the risk of haematoma or seroma under the graft, the wound bed might be sealed with fibrin glue, at the discretion of the surgeon.

The grafts will be fixed to the wound bed using a method at the discretion of the surgeon, including sutures, staples, or tissue glue (e.g. Histoacryl®, TissueSeal, Ann Arbor, Michigan).

A dressing that provides protection against sheering forces, keeps the study areas clean, is free of cytotoxic agents, and is not required to be changed prior to visit 4 (6-10 days) will be selected at the discretion of the surgeon (e.g. Mepilex Ag). The Coordinating Investigator can be contacted to discuss suitable wound dressings.

Photographic documentation will be carried out intraoperatively for both the control and experimental areas before and after wound bed preparation, and following application/fixation of the STSG and EHSG-KF.

In all patients, the surgical procedure ends after applying standardised dressings and/or splinting.

#### Delay of Treatment:

Delay of grafting can occur due to certain circumstances (e.g.):

- In the case of an inoperable patient due to standard criteria (e.g. high fever, high dose vasopressor/inotropic support, poor general condition), a severe infectious disease, cold or flu prior to skin grafting, scheduled surgery must be postponed until the patient has recovered
- EHSG-KF does not meet product specifications
- Any reason beyond the Investigator's or patient's influence leading to a delay of scheduled surgery

**CAUTION:** If surgery has to be delayed for >72 hours (from the time the product is packed in the GMP facility), graft stability is lost and it is no longer eligible for grafting. Tissue-engineering will again take approximately up to 38 days, varying individually due to biological activity of autologous cells and whether new IMP will be produced starting from a new skin biopsy or from previously harvested and stored cells. In acute cases, if surgery has to be postponed for >72 hours and therefore graft stability is lost, and if time does not allow a new graft to be manufactured from the cryopreserved cellular stock or from a second biopsy, the wound has to be covered applying the standard procedure of care and the patient has to be withdrawn from the study.

With special regard to any patients whose biopsy in the course of cell cultivation yields insufficient cell numbers or proliferation rates, which can be determined at the latest 10 days after the biopsy, the Investigator has to be immediately informed by the manufacturer. The patient and/or parent/legally authorized representative have to be informed by the Investigator immediately and an alternative therapeutic approach has to be offered appropriate to the patient's condition. If the patient and/or legally authorized representative freely agree, a second biopsy might be harvested for a new production procedure which can also be offered to the patient as a therapeutic approach. Results of the cell harvest and/or cellular proliferation assays, have to be recorded in the patient's tracking log by the manufacturer and the study

site. All steps performed thereafter have to be documented in the patient's records by the study site.

#### Management of Poor Graft Take Rate and Slow Epithelialization:

If assessment of graft take at visit 4 (day 6-10 after grafting) shows unsatisfactory results (graft take < 50%), or if assessment of time to complete epithelialisation shows unsatisfactory results (time to complete epithelialisation >8 weeks), the choice of further management is at the Investigators' discretion. According to the management of poor graft take in routine skin grafting, this could mean either conservative management (wound care, dressing changes) until the wound is closed secondarily and healed, or surgical closure by applying the standard of care for this individual situation and patient.

#### **7.3.6 Facultative Biopsies at Visit 3 (during Grafting)**

Facultative biopsies can be taken from each wound bed (experimental area and control area) before and after wound bed preparation (e.g. necrectomy, excision) prior to grafting for histological examination of the wound ground. The surgeon evaluates whether these biopsies are necessary.

- If applicable, this punch biopsy (2 – 3 mm diameter) in both study areas (experimental and control area) will be taken before preparing the wound bed for verification of the level of burn/defect depth. (Biopsies Nr. 2 and 3)
- If so, after preparing the wound bed, before grafting, another punch biopsy (2 – 3 mm diameter) will be taken in both areas to test wound bed quality for routine histology, immuno-histochemistry. This is performed for this study specifically. (Biopsies Nr. 4 and 5)

#### **7.3.7 Optional Biopsies at Visit 8 and 10 (~90 days and ~1 year after Grafting)**

Three months post-operatively and one year post-operatively, one representative optional punch biopsy (2 - 3 mm diameter) of each study area will be taken for routine histology and immuno-histochemistry. The results can be used for scientific dissemination, teaching purposes, and could become a part of the registration dossier of EHSG-KF for market authorisation.

If the patient/parents/legally authorized representative refuse to take the biopsies at Visit 8 and/or visit 10, this does not lead to withdrawal of the patient from the study.

#### **7.3.8 Photography**

At visits 3 to 12 digital photos of the study areas are taken. The standardised photographs will be taken according to the WI and provided to the Sponsor.

These photos will allow the surface area (cm^2) of epithelialization for the experimental and control areas to be determined with digital image analysis in order to determine the primary endpoint ratios. Quantification of the wounds will be assessed using either a site-specific computer-based analysis system or assessed by the Investigator. Parts of the experimental area that have epithelialized, or are covered with the healed study product, will be manually marked, measured, and considered as "covered surface area". This value will then be used to determine the primary endpoint as noted in chapter 8.1.

Additionally, the photos are used to document the course of the study of each patient, can be used for scientific dissemination, teaching purposes, and could become a part of the registration dossier of EHSG-KF for market authorisation.

The photos will be saved on a secure server, according to the WI of the Sponsor.

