#### 1.3.1 Benefits of EHSK-KF

- Minimal donor site area, relative to STSG. A small biopsy site of only 4 cm^2 (as precise as possible) is required to generate a 45 ± 4 cm^2 piece of EHSK-KF, while the ratio of graft size to donor site for a conventional STSG is approximately 1:1. Although the latter ratio can be increased through meshing, the amount of expansion achieved is consistently less than expected based on the meshing ratio, and STSG quality is sacrificed.
- By reducing the donor site area, the wound healing burden placed on the patient is reduced, along with the donor site morbidity, such as pain, pruritus, textural and pigmentation changes, infection, bleeding, delayed wound healing, and hypertrophic scar formation.
- Due to backup procedures during the manufacturing of the skin analogue, secondary and even further manufacturing phases can be achieved with only one biopsy, without recruiting new donor sites, and with minimal additional time. From a 4 cm^2 biopsy, two sheets (90 cm^2) can be generated in an average of 32 days (SD 4, range 26-38 days). In approximately 35-44 days, an estimated 1000 cm^2 (20 sheets) of EHSK-KF could be manufactured from the 4 cm^2 biopsy, and, in 38-48 days, an estimated 2000 cm^2 (40 sheets) could be generated, as calculated using doubling time data acquired in phase 1, thereby offering a potentially life-saving intervention in the setting of severe burns with limited donor sites (burns greater than 40% TBSA). Without the production of skin substitutes in the setting of severe burns with limited donor sites, definitive coverage of burns is delayed until the previously harvested donor site has healed (approximately 7-14 days) and can thus be re-harvested for further grafting. Moreover, a higher graft quality can potentially be achieved with the use of EHSK-KF, when compared with the widely meshed, often thinner grafts available for coverage in large burns.

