### 7.2.3 Visit 2 - Pre-treatment phase (Biopsy)

The following assessments have to be done prior to the biopsy harvest:

- Checking inclusion and exclusion criteria (still expected that  $\geq 90$  cm^2 of wound will remain open at 4 weeks post burn despite standard of care treatment; concomitant medical conditions; check results of screening laboratory tests and pregnancy test (if indicated))
- Vital signs (heart rate, temperature, blood pressure)
- Assessment/reporting of concomitant therapy
- Assessment/reporting of adverse events

In case the patient is eligible as required, a biopsy is performed.

- Skin biopsy (Biopsy Nr.1): Standard procedure of harvesting a split-thickness skin biopsy (or full-thickness skin biopsy in special cases after written confirmation of the manufacturer) of 4 cm^2 (as precise as possible)

In the case of a performed biopsy, but unsuccessful manufacturing process, a second biopsy can be harvested if the patient and/or parents/legally authorized representative consent to it.

In exceptional cases, at the discretion of the PI and after consultation with the Coordinating Investigator, the biopsy harvesting can be performed before the screening laboratory test results are available. This is based on the following rationale:

- HIV, HCV, HBV, and Syphilis screening laboratory is not performed for the patient's safety, but due to GMP regulation.
- HIV, HCV, HBV, and Syphilis test results must be available before the biopsy can be processed at the manufacturing site.
- In acute patients, time is very critical for the treatment process. Obtaining the screening results and shipping of the biopsy to the manufacturing site both usually take at least 24 hours each. Therefore, in severe burn patients, it can be in the interest of the patient to proceed with the biopsy harvesting without waiting for the screening laboratory, as long as the screening laboratory results will be available when the biopsy arrives at the manufacturing site.

Such procedure must be clearly documented in the Investigator Site File (ISF).

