## 8. Assessments of Endpoints

### 8.1 Primary Endpoint

#### 8.1.1 Skin Amplification

The primary endpoint, ratio of covered surface area to biopsy site/donor site surface area four weeks post grafting, was selected to test the hypothesis that EHSG-KF possesses greater skin amplification capabilities than split-thickness skin grafts. The covered surface area of the experimental and control areas refers to the total areas (in cm^2) that are healed, or epithelialized, and does not include areas characterized by open wounds.

The most important feature of EHSG-KF (being an engineered skin graft) is the fact that its use significantly reduces the harvest of large quantities of donor skin (standard of care) in burn patients for closure of burn injuries involving greater than 20% TBSA. The reduction in donor skin requirements implies reductions in donor site morbidity, numbers of skin-grafting operations, and intensive care days, but those data are not collected in this study since every patient received only 1 or 2 EHSG-KF. The chosen primary endpoint reflects this crucial feature by comparing the area that has “taken” on the wounds after 28 days in ratio to the size of the donor site harvested to graft.

Patients with large deep burns, particularly those involving greater than 40% total body surface area, have limited healthy skin graft donor sites. Clinicians face a dilemma in achieving definitive skin coverage in this patient population. As noted in chapter 1.1, current options, including widely meshed STSGs and CEAs, fall short of providing an optimal solution. An alternative to STSGs that can be expanded from a small, stamp-sized skin biopsy would help address this dilemma and thus carries the potential to reduce morbidity and mortality in severe burn patients. This capacity for expansion represents the primary medical benefit of the study product.

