Studies by Boyce et al. have similarly focused on this endpoint, demonstrating that the requirement for harvesting of donor skin for cultured skin substitutes (CSS) was less than for conventional skin autografts in patients with massive burns. Boyce et al. showed that CSS can be expanded by approximately 67 times, 66 times, and 108 times the area of donor skin, in the 2002, 2006, and 2016 studies, respectively, compared with an estimated value of 4 for 4:1 meshed autograft. In the latter study, the CSS was also shown to substantially reduce mortality when compared to a similar population from the National Burn Repository. The ratio of surface area covered at the experimental area to surface area biopsied, and the ratio of surface area covered at the control area to surface area harvested (i.e. control STSG donor site surface area) will be calculated at Visit 6 (28 ± 3 days post-grafting) and the two ratios will be compared. The covered surfaces areas (cm^2) for both the experimental and control sites will be determined using planimetric analysis at visit 6. Planimetric analysis will be used since the healed areas often have irregular shapes, with dimensions that are not conducive to measurement with a ruler.

In the absence of complications, such as hematomas and associated graft loss, four weeks should allow adequate time for healing of the STSG and EHSG-KF in order to reflect the long-term extent of coverage achieved by the two methods.

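### Skin closed by a later autograft before visit 6 counts as covered area, but its donor skin enters neither denominator of the primary ratio

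*Protocol*

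**What the plan says.** **Numerator.** Section 7.3.8 (Photography) defines the covered area with the clause "Parts of the experimental area that have epithelialized, or are covered with the healed study product, will be manually marked, measured, and considered as". The two conditions are joined by *or*, so epithelium need not come from the product. Section 8.1.1 applies to both areas and counts the parts "that are healed, or epithelialized, and does not include areas characterized by open wounds".

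**Denominator.** Section 8.1.1 defines the experimental ratio as "The ratio of surface area covered at the experimental area to surface area biopsied". For the control it uses the area harvested for the STSG, which 7.3.5 requires to be determined and recorded during the grafting operation.

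**Later closure.** Section 7.3.5, under the management of poor graft take, leaves treatment to the investigator when take at visit 4 (day 6-10) is below 50%. The options are conservative care "or surgical closure by applying the standard of care for this individual situation and patient". The rule is not limited to EHSG-KF. Section 9.7 also lists re-grafting operations among the ways complications are managed.

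**Who is analysed.** Patients who lose all of the EHSG-KF stay in the study until visit 10 (4.3.2). The primary analysis set is the mITT (10.3.1), with no exclusion for re-grafting.

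**Purpose.** The rationale in 8.1.1 describes the endpoint as the area that has taken after 28 days, relative to the donor site harvested for grafting.

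**The concern.** The endpoint is a yield: healed skin per cm² of donor skin. A re-graft adds healed area and also uses donor skin. The definitions credit the first and omit the second, so a re-grafted area scores a higher yield than it achieved under either sensible reading: coverage by the allocated graft alone, or coverage per all donor skin used.

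This matters because the ratio is the only confirmatory endpoint. It is tested on about 12 patients by a one-sample t-test on the log difference. Low take produces the extreme negative log differences in such a test. Replacing those values with near-complete coverage moves the mean and also shrinks the SD.

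**Working it through.** **The plan's own figure.** With a log difference of 0.90, SD 1.00 and two-sided 5% (10.2), exact one-sample t-test power is 81.0% at n = 12 and 76.7% at n = 11. The stated 12 is reproduced. The effect is also consistent: ln(7.35/3.00) = 0.896.

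**Time available.** Visit 4 is day 6-10 and visit 6 is day 25-31. A re-graft done at visit 4 has 25 - 10 = 15 to 31 - 6 = 25 days to heal.

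**One patient, one sheet.** From the protocol: sheet 45 cm², biopsy 4 cm², nominal control ratio 3.00. Assumed: 20% own healing, and the remainder closed by a 3:1 re-graft fully healed by visit 6.

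- Own healing: 0.20 × 45 = 9 cm². Re-grafted: 36 cm², using 36/3 = 12 cm² of donor skin.

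| Rule | Ratio | Log difference, ln(ratio/3.00) |
|---|---|---|
| As written | 45/4 = 11.25 | +1.32 |
| Product coverage only | 9/4 = 2.25 | -0.29 |
| All donor skin counted | 45/(4+12) = 2.81 | -0.06 |

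**Incomplete healing.** If 60% of the re-graft heals, the score is (9 + 21.6)/4 = 7.65 (+0.94). At 90% it is (9 + 32.4)/4 = 10.35 (+1.24).

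**Two sheets (90 cm²), same assumptions.** As written: 90/4 = 22.5 (+2.01). Product only: 18/4 = 4.50 (+0.41). All donor skin: 90/(4+24) = 3.21 (+0.07). Product coverage alone already exceeds control here. The break-even own take is 12/90 = 13.3%, against 12/45 = 26.7% with one sheet.

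**A re-grafted control area.** With 45 cm², the harvest is 45/3 = 15 cm². At 20% own healing the ratio is 9/15 = 0.60. It is scored 45/15 = 3.00 after re-grafting, and would be 45/27 = 1.67 with all donor skin counted. Against own coverage, the log gain from re-grafting is ln 5 = 1.61 in either area. Against the all-donor ratio, the overstatement is ln(16/4) = 1.39 for EHSG-KF and ln(27/15) = 0.59 for control.

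**Illustration for the test.** Simulation, n = 12, with only EHSG-KF areas re-grafted. Assumed: failing take 2-20%, other EHSG-KF sites 60-100% healed, control 80-100% healed, re-grafted area 80-100% healed. Four failures:

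| Sheets | Rule | Mean log difference | SD | P(success) |
|---|---|---|---|---|
| 1 | As written | 1.24 | 0.15 | 100% |
| 1 | All donor skin | 0.75 | 0.67 | 100% |
| 1 | Product only | 0.49 | 1.09 | 16% |
| 2 | As written | 1.93 | 0.15 | 100% |
| 2 | All donor skin | 1.26 | 0.94 | 100% |
| 2 | Product only | 1.18 | 1.10 | 99% |

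In this scenario, counting all donor skin changes the estimate more than the decision. With one sheet, exp(1.24) - 1 is about +246% and exp(0.75) - 1 about +112%.

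**The case against.** **No sentence says that re-grafted skin counts.** That is correct. It follows only from reading 7.3.5, 7.3.8 and 8.1.1 together, and the rationale in 8.1.1 points the other way. An unseen SAP could add a rule. Rescue treatment (3.7) and unscheduled visits (7.3.10) are already entered in the eCRF, so the event would be known. But the protocol itself fixes the numerator and denominator, and the rationale conflicts with those definitions without overriding them. The donor area of a re-graft is not listed for recording, and an SAP cannot recover an area that was never measured.

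**The direction is not established.** This stands. The take rule and the uncounted donor skin apply to control areas too, and the protocol gives no re-graft rates. A reader might infer that the primary test is biased towards success; the documents support only a conditional statement.

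**The example is a worst case.** This also stands. Full healing in 15-25 days is an upper bound, the 3:1 mesh for a re-graft is assumed, control is held at its nominal value, and conservative care is equally permitted.

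**Repeat biopsy.** Section 7.2.3 says that after failed manufacture "a second biopsy can be harvested if the patient and/or parents/legally authorized representative consent to it". A reader might infer that the second biopsy is left out and the ratio doubled. The text does not support that: the area biopsied can naturally include both, and new product may come from stored cells. It is worth a clarifying phrase, no more.

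**Conclusion.** The point holds as a defect in the definition of the primary endpoint. Area closed by a later autograft before visit 6 enters the numerator in either arm, and its donor skin enters no denominator, against the purpose stated in 8.1.1.

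In the one-sheet example, a patient at -0.29 on product coverage, or -0.06 with all donor skin counted, is scored at up to +1.32. That is the score of a perfect EHSG-KF graft. This rests on 20% own healing, a 3:1 re-graft fully healed by visit 6, and control at 3.00.

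The net bias is conditional. It favours EHSG-KF if EHSG-KF areas are re-grafted more often than control areas, and sufficiently frequent control re-grafting would offset or reverse it. It is smaller if re-grafts heal incompletely. With two sheets it matters less for the test, because product coverage alone more easily exceeds control. Its actual size cannot be derived, since the documents give no re-graft rates.

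**What to change.** 1. In 8.1.1, and by reference in 7.3.8, define each area's denominator as all donor skin harvested for that area up to visit 6. For EHSG-KF this is every biopsy taken to make the graft plus any re-graft harvest. For control it is the STSG harvest plus any re-graft harvest.
2. Record the re-graft donor area (cm²) and the study area it was used on in the eCRF.
3. Add a sensitivity analysis of the primary endpoint that counts surgically re-closed area as not covered, and state in advance how zero coverage is handled on the log scale.
4. Reconcile the wording of 7.3.5, 7.3.8 and 8.1.1 so that the definition matches the stated purpose.

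The cost is a wording change, one eCRF field and a possibly less favourable estimate. Nothing changes in how a poorly taking graft is treated.
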